### Control: Standard care

Caregivers in the control arm will receive the existing clinic-based HRSN screening and referral procedures as currently implemented, without access to the chatbot. These caregivers will complete the same study assessments as the intervention group except those related to chatbot usability and feasibility of the intervention.

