### Contamination and standard care

To minimize contamination, intervention access will be restricted to unique participant credentials, and control participants will not be provided DAPHNE links or onboarding materials. At each follow-up assessment (1, 3, and 6 months), participants will be asked whether they have used DAPHNE outside the study or accessed any other digital HRSN screening tools. Any reported cross-exposure will be documented.

Usual care will be characterized and documented systematically. At study initiation, we will document clinics describing current HRSN screening instruments, workflow roles (e.g., medical assistant, nurse, social worker), timing of screening, referral pathways, and EHR documentation practices (where applicable). In addition, EHR abstraction will include primary care visits, number of missed appointments, number of ER visits, HRSN screening and referrals (social work encounters) for all participants. Follow-up calls with caregivers in the standard care arm will capture services received outside the health system (e.g., community-based referrals not documented in the EHR). These procedures will allow comparison of intervention and standard care exposure.

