#### Secondary outcomes.

Secondary outcomes address caregiver- and provider-level effects. Caregiver-reported outcomes (cPROMs) include stress [55], self-efficacy [56], satisfaction with access to community resources [57], and quality of life for caregiver and child as proxy [58]. These cPROMs will be completed by caregivers in both arms at baseline, 3, and 6 months. In addition to cPROMs, caregivers in both arms will complete the standardized HRSN screener. This survey will be administered at 3 and 6 months to capture changes in reported needs over time. Caregiver engagement with the chatbot is measured through system logs (e.g., minutes of use, number of logins, session durations, screenings completed, and resources accessed). Caregiver burden associated with study procedures will be measured in both arms using the Participant Burden Assessment (PeRBA; target ≥4) at 1, 3, and 6 months [59]. Provider perspectives on workflow integration will be assessed using the Workflow Integration Expectancy tool, with a target rating ≥ 4 [60]. These secondary outcomes will be analyzed to see how they change over the course of the trial and to eventually address whether there are any associations with outcome changes and chatbot use.

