### Sample size justification

This pilot trial is designed to estimate feasibility parameters rather than to test clinical efficacy. A prespecified feasibility benchmark is 6-month retention ≥70% (proportion of randomized caregivers completing the 6-month assessment). This target was selected because retention is a conservative, study-wide indicator of feasibility for a 6-month caregiver-facing digital intervention and provides guidance for assessing the viability and planning parameters of a future trial. Consistent with the ORBIT framework, this benchmark will inform, rather than solely determine, decisions regarding refinement of study procedures and progression to a larger efficacy study.

With n = 100 randomized caregivers, if retention is 70%, the corresponding 95% confidence interval (Wilson method) [62] will have an expected half-width of approximately ±9 percentage points, providing sufficient precision to inform decisions for a future trial.

For secondary outcomes, the intervention arm will allow estimation of mean SUS scores with acceptable precision. Assuming a standard deviation of approximately 12–15 points, the 95% confidence interval for the mean SUS will have an expected half-width of approximately ±3–6 points. Confidence intervals for proportions will be calculated using Wilson intervals, and confidence intervals for continuous outcomes will use t-based methods (or bootstrap methods if distributional assumptions are not met).

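### Calls about help received outside the health system are described for the standard-care arm only, so the stated between-arm comparison of exposure rests on unequal measurement

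*Protocol article*

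**What the plan says.** The section Contamination and standard care describes several sources on what caregivers receive.

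- **Health record, both arms.** Abstraction includes "HRSN screening and referrals (social work encounters) for all participants".
- **Cross-exposure question, both arms.** At 1, 3 and 6 months, "participants will be asked whether they have used DAPHNE outside the study or accessed any other digital HRSN screening tools".
- **Calls, one arm named.** "Follow-up calls with caregivers in the standard care arm will capture services received outside the health system", with community referrals missing from the EHR given as the example.

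The paragraph then concludes: "These procedures will allow comparison of intervention and standard care exposure".

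Two other sections bear on the point. Control: Standard care says: "These caregivers will complete the same study assessments as the intervention group except those related to chatbot usability and feasibility of the intervention". Secondary outcomes says: "Caregiver engagement with the chatbot is measured through system logs", and lists examples such as time in the app, logins, screenings and resources opened.

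**The concern.** The chatbot exists to link families to community resources, and much of that help never appears in a hospital record. The plan measures it by direct questioning in one arm and has nothing comparable in the other, then says the arms can be compared. Caregivers in the DAPHNE arm also receive standard care, so they too can get community referrals that the EHR misses.

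An observed difference in outside-system exposure would mix any true difference with the difference in how it was looked for. The Future directions section says pilot estimates will inform endpoint selection and names referral uptake as a likely secondary outcome of the next trial. A distorted contrast could therefore be carried forward.

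**Working it through.** **Step 1. Does any source give the DAPHNE arm an equivalent measure?**

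| Source (section of the protocol article) | Arms | Shows outside-system services received? |
|---|---|---|
| EHR abstraction (Contamination and standard care) | both | No, in-system only |
| Question on DAPHNE or other digital tools (same section) | both | No, tool use only |
| Follow-up calls (same section) | standard care named | Yes |
| HRSN screener, 3 and 6 months (Secondary outcomes) | both | No, needs only |
| Satisfaction with resource access, baseline, 3 and 6 months (Secondary outcomes) | both | No, a rating |
| Chatbot logs (Secondary outcomes) | DAPHNE | No, in-app activity only |
| Qualitative interviews (Procedures; Primary outcome) | both, 10 caregivers | In part, a small subsample |

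None does so systematically. The Control section defines the control assessments as those of the intervention group less the chatbot items, which adds no call for the DAPHNE arm.

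**Step 2. Is it fair to read the calls as one-sided?** The text names one arm and does not expressly exclude the other. The neighbouring sentences refer to participants generally, or to all of them, when both arms are meant. Reading the calls as confined to standard care is therefore an inference, but a reasonable one.

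**Step 3. The plan's own figure.** The only sample-size basis is the Wilson 95% interval for 70% retention with n = 100. The half-width is z√[p(1−p)/n + z²/(4n²)] / (1 + z²/n). With z = 1.96, p = 0.70 and n = 100 this gives 0.088, an interval of 60.4% to 78.1%. That agrees with the stated ±9 points, and nothing in this point alters it.

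**Step 4. What unequal capture can do.** The documents give neither the rate of outside-service receipt nor any capture rate, so every input here is an assumption. Let p be the true proportion receiving such help, equal in both arms, and let s be the share captured.

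Observed difference (DAPHNE − standard care) = p × (s_DAPHNE − s_control).

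With s_control = 90%:

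| s_DAPHNE | p = 20% | p = 40% | p = 60% |
|---|---|---|---|
| 90% | 0 | 0 | 0 |
| 60% | −6 | −12 | −18 |
| 30% | −12 | −24 | −36 |
| 0% | −18 | −36 | −54 |

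(Percentage points.) For example, 0.40 × (0.60 − 0.90) = −0.12.

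**Step 5. The sign is not fixed.** Suppose a log entry is counted as receipt, and a share f of DAPHNE caregivers who received nothing have such an entry. The difference becomes p(s_DAPHNE − s_control) + (1 − p)f, which is zero at f = p(s_control − s_DAPHNE)/(1 − p). With p = 40% and s_DAPHNE = 60%, f = 0.12/0.60 = 20%. With s_DAPHNE = 30%, f = 0.24/0.60 = 40%. Above those values the false difference favours DAPHNE.

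**Step 6. With equal capture.** If s is the same in both arms, the observed difference is s × (p_DAPHNE − p_control). It is zero when true receipt is equal and keeps the right sign otherwise.

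**The case against.** The case on the other side has real force on consequence.

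- **Outside-service receipt is not a listed outcome.** It appears among none of the primary, secondary or exploratory outcomes. The comparison is descriptive, and the between-arm models are declared exploratory. This stands and limits the severity.
- **Describing usual care is not harmed.** A reader might infer that the third study objective, characterising the current standard of care, is biased. The documents do not support this. That objective needs data from the usual-care arm, which is where the calls are made.
- **Retention.** A reader might infer that calls to one arm raise its retention, a primary feasibility measure. The article does not give the timing of the calls or say they are extra contacts; they could coincide with the scheduled assessments. The DAPHNE arm has its own onboarding and weekly notifications. The benchmark is the "proportion of randomized caregivers completing the 6-month assessment", taken over all 100 caregivers and not as an arm contrast. An effect is possible but not shown.
- **Direction.** A reader might infer a bias against DAPHNE. As Step 5 shows, this depends on how log entries are treated, which the article does not say.
- **Other symmetric measures exist.** Satisfaction ratings, the HRSN screener and the interviews cover both arms. They give context but do not count services received.
- **This is a condensed article.** Its table of endpoints and instruments (S1 Table) is not at hand and could hold a matching item. But the article itself states the procedure, names the arm and asserts what the procedure permits, so the mismatch is in the text as published.

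None of this rescues the closing claim that the procedures support a comparison of exposure between arms.

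**Conclusion.** The point holds in a limited form: should-fix. As written, the plan measures outside-system services by calls in one arm and has no equivalent systematic measure in the other, so its descriptive between-arm comparison of that exposure is distorted by unequal ascertainment. The in-system part of the comparison, from the EHR, is measured alike in both arms and is not in question.

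The documents do not allow the size or direction to be determined. Under-capture would understate DAPHNE-arm receipt; counting log entries as receipt would overstate it. The figures above illustrate the mechanism under assumed rates and are not estimates for this trial. The conclusion rests on reading the calls as confined to the arm named.

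**What to change.** **Preferred.** Replace the sentence on calls with wording such as: *At 1, 3 and 6 months, caregivers in both arms will answer the same structured questions on referrals made and services obtained from outside the health system, by the same mode and over the same recall window.* Put the items in the follow-up assessments that both arms already complete. Base the exposure comparison on these items and the EHR, and keep the chatbot logs as a description of the DAPHNE arm.

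**Alternative.** Keep the calls in the standard-care arm, state that they serve only to describe usual care, and remove the claim that they allow the arms to be compared on outside-system services.

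**Cost.** The preferred change needs a few extra survey items and a short amendment. Identical questions remove the difference in instrument; they do not remove any reporting difference that arises because caregivers know whether they have the chatbot. Study status and timeline says enrolment is active, so an early change is better: follow-up points already passed can be filled only by longer recall.

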### Procedures

All caregivers will complete caregiver-reported outcome measures (cPROMs; see “secondary outcomes” section below) at baseline, 3 months, and 6 months post-intervention. Demographic information will be collected from all caregivers at baseline. Intervention group participants will have on-demand access to the chatbot throughout the 6-month study period, and will receive weekly notifications from the chatbot app. 10 caregivers from both groups will also complete a qualitative interview at 3 months and 6 months to evaluate their experience using the chatbot app versus receiving the standard of care.

### Provider component

After receiving a brief demonstration of the DAPHNE chatbot, providers will share their feedback and complete a structured survey on current HRSN screening and referral practices. Providers will complete the Workflow Integration Expectancy (WIE) tool and the Feasibility of Intervention Measure (FIM) at baseline and 6 months; providers will also complete the SUS at baseline. Additionally, providers will complete a survey on the feasibility of implementing the chatbot into their clinical workflows at baseline and 6 months. Semi-structured interviews will be conducted to elicit feedback on integration challenges, potential facilitators, and perceived impact on team workflow. Data from provider surveys will be analyzed descriptively, and interview transcripts will undergo thematic analysis to identify patterns in feasibility, barriers, and opportunities for scaling.

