### Study objectives

The long-term goal of this research is to develop an empirically supported, scalable, AI-driven solution to facilitate HRSN identification and referral in pediatric primary care. This pilot study has three specific objectives: (1) To assess the feasibility, acceptability, and usability of the DAPHNE chatbot with caregivers and providers of pediatric primary care patients compared with standard care; (2) To evaluate the feasibility and acceptability of the study protocol, including recruitment, retention, and measurement strategies, for informing design of a future large-scale trial; and (3) To characterize the current standard of care for addressing unmet HRSNs, thereby informing selection of appropriate comparator conditions and outcomes in future trials.

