## Methods

### Study design and setting

This study is designed as a pilot randomized controlled trial (pRCT) guided by the ORBIT model (Phase IIb) [32,33]. One hundred caregivers of children (prioritizing ≤2 years of age) will be recruited from Nationwide Children’s Hospital Primary Care Network (NCH PCN). Following baseline assessment, participants will be randomized in a 1:1 ratio to either the standard care group or DAPHNE + standard of care group (n = 50 per arm). In addition, 10 providers will be recruited to complete surveys on workflow integration and HRSN practices.

The trial will be conducted in NCH PCCs, which provided nearly 250,000 visits in 2024 for mostly Medicaid-enrolled patients. The PCN includes 14 clinics across the Columbus metropolitan area. For the purpose of this study, we identified clinics with the capacity to support the research project and a relatively higher number of patients with unmet HRSNs.

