### Participants

Caregivers. Recruitment will occur through the NCH PCN, with research staff approaching caregivers during routine visits. Our target recruitment is n = 50 participants per arm, facilitated using flyers and social worker referrals. Furthermore, we will communicate with potential participants who are interested via virtual methods (phone call, teleconference). Inclusion criteria are: (1) primary caregiver of a child (prioritizing ≤2 years old) receiving care at the selected clinics in the PCN, (2) self-identify with at least one unmet HRSN (3) ability to provide informed consent and complete study surveys in English, (4) ownership of a mobile device for chatbot use, and (5) willingness to participate in follow-up assessments. Exclusion criteria: none beyond failure to meet the above criteria. Caregivers will be compensated for their participation.

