#### Providers.

To evaluate the feasibility of integrating the DAPHNE chatbot into clinical workflows at primary care clinics, we will recruit approximately 10 providers across the NCH PCN, ensuring representation from at least 50% of the 14 PCC sites. Eligible providers include physicians, nurses, social workers, and care coordinators who are directly involved in patient care. Providers on extended leave or those not engaged in patient care will be excluded. Recruitment will be facilitated through the NCH Primary Care Research Network.

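### The provider survey of current HRSN practice follows the DAPHNE demonstration, leaving one input to objective 3 open to an avoidable order effect (minor)

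*Protocol article*

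**What the plan says.** The third aim under Study objectives is "To characterize the current standard of care for addressing unmet HRSNs", so that comparators and outcomes can be chosen for later trials. The Discussion names provider surveys, together with EHR data, as material for that description.

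The Provider component section sets the sequence: "After receiving a brief demonstration of the DAPHNE chatbot, providers will share their feedback and complete a structured survey on current HRSN screening". The same survey also covers how referrals are made. The section describes no provider survey of existing practice before the demonstration. It also schedules the SUS at baseline, and the FIM and the Workflow Integration Expectancy tool (WIE) at baseline and 6 months. Provider surveys are to be analysed descriptively.

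On who is surveyed, the Providers section states: "we will recruit approximately 10 providers across the NCH PCN, ensuring representation from at least 50% of the 14 PCC sites". Eligibility depends on role and patient contact: "Eligible providers include physicians, nurses, social workers, and care coordinators who are directly involved in patient care". Working at a clinic that enrols caregivers is not a condition. Caregivers, by contrast, must have a child "receiving care at the selected clinics in the PCN", and Study design and setting explains how those clinics were chosen: "we identified clinics with the capacity to support the research project and a relatively higher number of patients with unmet HRSNs".

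**The concern.** A question about what a clinic does now can be answered without any knowledge of DAPHNE. Asking it after the tool has been shown means each provider describes existing screening and referral with an alternative freshly in mind. That can shift answers by contrast (present practice looks thinner than it would have) or by demand (the provider leans towards what the study seems to want). Once a provider has seen the tool, an unexposed answer cannot be recovered.

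What is at stake is the survey's share of objective 3, and so part of the evidence for choosing the next trial's comparator.

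A second, smaller matter concerns whose practice is described. Enrolling clinics were chosen partly for having more patients with unmet needs, a feature plausibly related to how they screen and refer. Providers from other clinics may describe a different usual care. They may also give 6-month FIM and WIE ratings with the demonstration as their only described contact with DAPHNE.

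**Working it through.** The plan states no figure for this point, so there is none to reproduce. The check has three parts.

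**1. Does anything require the demonstration to come first?**

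| Provider instrument | Needs knowledge of DAPHNE? | Place in the text |
|---|---|---|
| Structured survey of current screening and referral | No | After the demonstration |
| SUS | Yes | Baseline |
| FIM | Yes | Baseline and 6 months |
| WIE | Yes | Baseline and 6 months |

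Only the last three need the demonstration. The practice survey could precede it without loss. The text clearly places the demonstration first; it joins feedback and survey with a simple conjunction, so the order of those two is not fixed.

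**2. How much of objective 3 rests on the survey?** The document gives these sources on usual care:

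- Provider survey (Provider component): after the demonstration.
- Documentation of clinics' instruments, workflow roles, timing, referral pathways and EHR practices (Contamination and standard care): at study start, not tied to the demonstration.
- EHR abstraction of screening and referrals (same section): all participants.
- Follow-up calls on services received outside the health system (same section): control-arm caregivers.
- Qualitative interviews on the current standard of care (Primary outcome): control-arm caregivers.

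The provider survey is one of five sources, and the last three come from trial participants. None of the other four is tied to the provider demonstration.

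**3. How many providers could work outside the enrolling clinics?** Inputs: 14 sites, at least 50% represented, about 10 providers (taken as 10). The number of enrolling clinics, k, is not stated and is treated as an assumption from 1 to 14.

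- Minimum sites represented = 0.5 × 14 = 7.
- Minimum represented sites outside the trial = max(0, 7 − k). With at least one provider per represented site, at least that many of the 10 providers are outside.

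| Assumed k | Minimum outside sites (and providers of 10) |
|---|---|
| 1 | 7 − 1 = 6 |
| 3 | 7 − 3 = 4 |
| 5 | 7 − 5 = 2 |
| 6 | 7 − 6 = 1 |
| 7 to 14 | 0 |

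For k from 7 to 13, outside providers are not forced, but nothing rules them out. At k = 14 there is no outside clinic. The extent therefore cannot be settled from the document; what can be said is that the sampling rule permits a mismatch.

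**The case against.** The strongest reply is that the plan does not rely on this survey alone. The Contamination and standard care section sets out a systematic description of usual care, and control-arm interviews add to it. Under-reported screening in the survey could be checked against the EHR and the clinic documentation. This stands, and it limits the point to one supporting input. It does not remove the point: the EHR shows only what was documented, calls and interviews give the caregiver's view, and the survey still enters the account of standard care.

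It can also be said that the survey is structured and descriptive, and that nothing shows its answers will be distorted. That is right. A reader might infer that the provider account is already biased, that the developers run the session, or that DAPHNE is presented to providers as the remedy for present practice. The text says none of this; it mentions only a brief demonstration and does not say who gives it.

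On sampling, breadth across the network is a defensible choice. The provider sample is meant to assess workflow integration in primary care clinics, and Future directions foresees a multi-site trial. By its name, the WIE measures expectation, and the document does not require raters to have had a patient using DAPHNE. A rule of one provider per enrolling clinic might be unworkable: with 10 providers it fails if k exceeds 10. These arguments stand. They leave no case for changing recruitment, only for reporting by enrolling status.

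**Conclusion.** The point holds as a minor one. The order of demonstration and practice survey exposes one input to objective 3 to an order effect that the design could avoid at almost no cost. It applies to every provider surveyed under the sequence described, but its direction and size are unknown. It does not touch any comparison between arms.

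Two stronger conclusions are tempting and not supported. One is that the trial will fail to describe its comparator: four other sources bear on usual care, three of them drawn from participants. The other is that providers will come from outside the trial clinics: that is forced only if k is 6 or fewer, and k is not given. Nor does the sampling rule make the 6-month FIM and WIE ratings invalid; it makes it useful to know which raters worked where DAPHNE was in use.

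The conclusion rests on the article's text. The time-schedule figure and the supporting table of endpoints were not available for this check; if either places the practice survey before the demonstration, the text should be aligned with it and the order concern falls away.

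**What to change.** 1. In Provider component, move the structured survey of current screening and referral ahead of the demonstration. Follow it with the demonstration, then SUS, FIM and WIE.
2. The Study status and timeline section reports that enrolment is active, without saying whether this includes providers. For any provider already surveyed, report the order used.
3. Record whether each provider works at a clinic that enrols caregivers. Show the survey-based description of standard care, and the 6-month FIM and WIE, descriptively by that status. Leave the network-wide recruitment rule unchanged.

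The cost is a slight resequencing of one visit and one extra data item, with the same roughly 10 providers and the same instruments. The downside is that the subgroups by enrolling status will be very small, so they can only be described, not compared.
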